## Abstract

**Background:**

The treatment of patients with malignant brain tumors remains a major oncological problem. The median survival of patients with glioblastoma multiforme (GBM), the most malignant type, is only 15 months after initial diagnosis and even less after tumor recurrence. Improvements of standard treatment including surgery and radio-chemotherapy have not lead to major improvements. Therefore, alternative therapeutics such as oncolytic viruses that specifically target and destroy cancer cells are under investigation. Preclinical data of oncolytic parvovirus H-1 (H-1PV) infection of glioma cells demonstrated strong cytotoxic and oncosuppressing effects, leading to a phase I/IIa trial of H-1PV in patients with recurrent GBM (ParvOryx01). ParvOryx01 is the first trial with a replication competent oncolytic virus in Germany.

**Methods:**

ParvOryx01 is an open, non-controlled, two groups, intra-group dose escalation, single center, phase I/IIa trial. 18 patients with recurrent GBM will be treated in 2 groups of 9 patients each. Treatment group 1 will first receive H-1PV by intratumoral injection and second by administration into the walls of the tumor cavity during tumor resection. In treatment group 2 the virus will initially be injected intravenously and afterwards, identical to group 1, into the surrounding brain tissue during tumor removal. Main eligibility criteria are: age of 18 years, unifocal recurrent GBM, amenable to complete or subtotal resection. Dose escalation will be based on the Continual Reassessment Method. The primary objective of the trial is local and systemic safety and tolerability and to determine the maximum tolerated dose (MTD). Secondary objectives are proof of concept (PoC) and Progression-free Survival (PFS) up to 6 months.

**Discussion:**

This is the first trial with H-1PV in patients with recurrent GBM. The risks for the participants appear well predictable and justified. Furthermore, ParvOryx01 will be the first assessment of combined intratumoral and intravenous application of an oncolytic virus. Due to its study design the trial will not only generate data on the local effect of H-1PV but it will also investigate the penetration of H-1PV into the tumor after systemic delivery and obtain safety data from systemic delivery possibly supporting clinical trials with H-1PV in other, non-CNS malignancies.

**Trial registration:**

ClinicalTrials.gov Identifier: NCT01301430

## Background

According to the estimation of the American Cancer Society about 16,000 new cases of intracranial neoplasm are diagnosed in the USA each year, being over half the number of new cases of melanoma [1]. The largest group with approximately 12,700 new cases per year are gliomas, primary central nervous system neoplasms with characteristics of neuroglial cells. Of those the most frequent subgroup with more than 6,000 new diagnoses per year is glioblastoma multiforme (GBM), which is also the most malignant type of gliomas. The incidence of GBM is currently showing a slight but relevant increase [2]. The majority of patients diagnosed with GBM is over 40 years of age [1].

Despite different therapeutic approaches and their recent progress, the treatment options for patients suffering from glioblastoma are still disappointing. The overall survival rates amounted to 33, 12, 7, 5, and 4 per cent after 1, 2, 3, 4, and 5 years, respectively [3]. The 1-year PFS was as low as 10% in individuals presenting recurrent disease and treated solely with chemotherapy [4]. At present, established therapeutic strategies include surgery, radiation, chemotherapy, and molecular targeted agents. New approaches are on the way [5].

Amongst other experimental therapies, oncolytic viruses are investigated for treatment of high-grade gliomas. Several candidates such as HSV-1, adenovirus, Newcastle disease virus, reovirus, poliovirus, and vaccinia virus were identified to have toxic effects on glioma cells [6]. Up to now several clinical trials were carried out to demonstrate the safety and in part efficacy of the viral candidates in patients suffering from recurrent malignant gliomas [7-11]. All viruses were administered either intratumorally or intracerebrally into the walls of the resection cavity. A good tolerability and no safety issues could be observed throughout the trials. If applicable, the dose escalation could be performed according to the predefined schedule.

## Trial rationale/justification

Agents that possess anti-glioma activity, a tolerable safety profile and no unjustified risk for the general population should undergo rapid development to assess their therapeutic potential.

Parvovirus H-1 (H -1PV) is a small single-stranded rodent DNA virus. The natural host is rat but H-1PV is able to infect and replicate in cells of various other species including humans. Parvoviruses are unique among DNA viruses as they do not have any tumorigenic members [12]. In contrast, some parvoviruses exert cytopathic effects, mainly in neoplastic cells [13] and they have been shown to possess oncosuppressive properties [14,15]. In general, parvovirus H-1 is classified as non pathogenic.

A strong oncolytic effect was shown in different established glioblastoma cell lines of rat and human origin and in short-term/low-passage cultures of human glioblastoma cells, at low multiplicities of infection (MOI) [16]. Infection of glioma cells with H-1PV virus yielded progeny H-1PV virions in all cultures, however with marked differences of titers. In conclusion, malignant glial cells appear to represent a highly susceptible target for H-1PV virus-mediated cytotoxicity. Furthermore, H-1PV was shown to activate a non-conventional, cathepsin-mediated death pathway, leading to cell killing also in glioma cells that are frequently resistant to apoptotic cell death mechanisms [17].

In orthotopic glioma models in rats large tumors (> 6 mm) were either injected stereotactically with H-1PV (single intratumoral injection) or H-1PV was administered by multiple intravenous injections (systemic route). H-1PV virus treatment resulted in rapid tumor regression and significant prolongation of survival of treated animals [18]. Histological analysis showed widespread destruction of tumor tissue, without any toxic or inflammatory side effects in the surrounding brain tissue. Virus replication was demonstrated in tumors, indicating a contribution of secondary infection by progeny virus to the efficiency of oncolysis. Hence, complete remission of advanced intracranial gliomas by oncolytic parvovirus H-1PV could be achieved showing that H-1PV possesses strong anti-tumor activity also in vivo.

Based on the findings described above, H-1PV may be reasonably assumed to be effective for treatment of glioblastoma in humans. Moreover, the virus offers some potential advantages over the current therapeutic modalities:

Unlike other oncolytic viruses, H-1PV was shown to cross the blood-brain barrier and to infect intracerebral tumors. This offers the chance of boosting the initial local therapy by consecutive intravenous administrations or for interval retreatment without the necessity of craniotomy.

H-1PV may potentially evoke an anticancer vaccination effect based on release of tumor-associated antigens and subsequent immunostimulation. This could lead to long-term effects in prevention of disease relapse, potentially adding to initial oncolysis.

Taken together, the therapy with H-1PV as planned in this protocol may provide considerable benefit for included subjects. Furthermore, the findings from the trial are crucial for consecutive clinical development of H-1PV for glioblastoma and other tumor entities.

## Design and methods

### Aim

This trial aims to investigate the safety, biodistribution, maximum tolerated dose and signs of anti-tumor activity of parvovirus H-1 in patients suffering from recurrent malignant gliomas. According to preclinical data and differing from previous oncolytic virus trials in GBM patients ParvOryx01 will not only include intratumoral virus application but also intravenous treatment.

### Objectives

#### Primary objectives

The primary objective of the trial is related to the safety and tolerability of the Investigational Medicinal Product (IMP). The particular parameters for this objective are:

• Local and systemic safety and tolerability of intratumoral/intracerebral and intravenous/intracerebral administration of the IMP,

• Maximum tolerated dose (MTD) of the IMP as assessed by NCI CTCAE v4.0,

• Viremia following intratumoral, intracerebral and intravenous administration of the IMP,

• IMP shedding/persistence following intratumoral, intracerebral and intravenous administration of the IMP.

#### Secondary objectives

The secondary objective of the study is related to the efficacy of the IMP. The particular parameters for this objective are:

• Evidence for anti-tumor activity of the IMP in subjects with recurrent GBM (Proof of Concept, PoC),

• Progression-free Survival (PFS) up to 6 months after study inclusion,

• Overall survival (OS) up to 6 months after study inclusion.

### Design

Parvoryx01 is an open, non-controlled, two groups, intra-group dose escalation, single center study.

Due to the exploratory approach of the current trial with regard to safety and tolerability of the IMP no positive control will be used. The implementation of a negative control (placebo) is ethically unjustifiable in subjects suffering from rapid progressive disease who otherwise can undergo a potentially effective treatment.

The safety and tolerability of the IMP will be investigated after both, local, i.e. intratumoral/intracerebral and systemic, i.e. intravenous administration. Therefore, two separate study groups representing both modes of administration will be examined. Since the trial is the first-in-man study of the IMP, the dose escalation will be carried out in accordance to a sequential escalating design, including interims assessments of safety and tolerability after each dose level and between both study groups.

Due to the complex handling and administration of the IMP this first trial will be performed in a single center under coordination of an investigator who possesses profound knowledge of all aspects concerning the IMP.

### Eligibility

Patients have to suffer from progressive primary or recurrent glioblastoma multiforme (GBM) scheduled for neurosurgery, i.e. for a complete or subtotal tumor resection. Patients have to fulfill the following main inclusion crieteria: (i) 18 years of age or older, (ii) confirmed diagnosis of glioblastoma multiforme (WHO grade IV), (iii) recurrence or tumor progression despite previous radio- and/or chemotherapy, (iv) life expectancy of at least 3 months, (v) Karnofsky Performance Score ≥60, (vi) commitment to omit exposure to infants < 18 months of age or immunocompromised individuals for up to 28 day after first administration of IMP.

Main criteria to exclude subjects from the trial are (i) multifocal disease, (ii) evidence of distant tumor metastases, (iii) contraindications for MRI, (iv) treatment with antiangiogenic substances within 21 days prior to therapy, (v) radiotherapy within 90 days prior to study inclusion, (vi) chemotherapy within 4 weeks prior to study inclusion.

### Sample size

The current trial represents the first in man study with the IMP (ParvOryx). 18 subjects will be allocated to 2 study groups with 9 subjects per group. Per group, 3 dose levels will be investigated. The mean number of 3 subjects per dose level appears to be sufficient to give first indications about safety, tolerability and proof of concept of ParvOryx.

There will be no a-priori defined quantitative ratio between females and males. However, no gender differences in the safety, tolerability as well as efficacy are expected on the basis of preclinical findings.

### Course of the trial

For each patient the ParvOryx01- trial includes two phases: i) the screening phase in which eligibility for trial inclusion is assessed and ii) the treatment/follow-up phase in which the trial treatment, the medical monitoring and 3 follow-up visits are performed. Due to the rapid growth of recurrent glioblastomas and the limited capacity for fast consecutive study inclusion according to safety regulations, patients have to be continuously screened while other patients are already under treatment. Therefore, screening phase and treatment phase are overlapping.

#### Screening phase

Screening of patients has to be performed within 2 weeks prior to study inclusion. Potentially eligible patients are provided with comprehensive written and verbal information. Investigations that are carried out during the screening procedure include:

Written informed consent, demography and medical history, physical and neurological examination, vital signs and 12-lead ECG, clinical chemistry, hematology and clotting, serum protein electrophoresis, MRI, viral shedding of H-1 PV in blood, urine, stool and throat swabs, H-1 PV specific antibodies, HIV, HBV and HCV serology, pregnancy test.

At discretion of a responsible investigator patients in group II can be required to undergo a stereotactic biopsy and sampling of a tumor specimen for histological confirmation of GBM by a neuropathologist (only, if in opinion of the investigator the evidence of glioblastoma recurrence is not sufficient).

#### Intervention

The IMP for this trial is ParvOryx, a GMP-grade preparation of Parvovirus H-1. The application of the IMP will be performed in 2 groups of 9 patients each. The route of administration differs between group 1 and group 2 (Figure 1). Within each group the mode of application is identical, but the dose will be increased if no dose limiting events are observed. In each group the IMP will be administered in three dose levels (Table 1)

**Figure 1 F1:**
[figure not shown]
**Schematic diagram of the ParvOryx01 trial: study group 1 will be treated first**. After completion of group 1 an interim analysis will be performed prior to recruiting patients for study group 2. Information about dose escalation is specified in Table 1.

**Table 1 T1:** Dose schedule for both study groups

GROUP I			
Escalation Level	Study Time	Dose and route of administration	Duration
**Level 1** Total dose: 1 × 10^6 ^pfu	Day 1	5 × 10^5 ^pfu, intratumoral (via catheter)	15 minutes
	
	Day 10	5 × 10^5 ^pfu, intracerebal (direct injection at multiple locations of resection wall)	15-30 minutes

**Level 2** Total dose: 5 × 10^7 ^pfu	Day 1	2.5 × 10^7 ^pfu, intratumoral (via catheter)	15 minutes
	
	Day 10	2.5 × 10^7 ^pfu, intracerebal (direct injection at multiple locations of resection wall)	15-30 minutes

**Level 3** Total dose: 1 × 10^9 ^pfu	Day 1	5 × 10^8 ^pfu, intratumoral (via catheter)	15 minutes
	
	Day 10	5 × 10^8 ^pfu, intracerebral (direct injection at multiple locations of resection wall)	15-30 minutes

GROUP II			
**Escalation Level**	**Study Time**	**Dose and Route of Administration**	**Duration**

**Level 1 **Total dose: 1 × 10^6 ^pfu	Day 1 - 5	1 × 10^5 ^pfu, intravenous infusion	2 hours
	
	Day 10	5 × 10^5 ^pfu, intracerebral (direct injection at multiple locations of resection wall)	15-30 minutes

**Level 2** Total dose: 5 × 10^7^	Day 1 - 5	0.5 × 10^7 ^pfu, intravenous infusion	2 hours
	
	Day 10	2.5 × 10^7 ^pfu, intracerebral (direct injection at multiple locations of resection wall)	15-30 minutes

**Level 3 **Total dose: 1 × 10^9 ^pfu	Day 1 - 5	1 × 10^8 ^pfu, intravenous infusion	2 hours
	
	Day 10	5 × 10^8 ^pfu, intracerebral (direct injection at multiple locations of resection wall)	15-30 minutes

Specification of virus application and dose escalation during the Parvoryx01 trial: dose group 2 will be treated after completion of group 1 and after interim analysis of safety and tolerability in group 1.

In group 1 the patients will receive the IMP on day 1 via image guided injection into the tumor tissue. On this day the patient is injected with 50% of the intended overall dose. After an observation period of 9 days the tumor will be resected on day 10. After tumor removal the second half of the dose will be administered into the walls of the resection cavity by direct injection. With this injection during open surgery the administration of the IMP is completed and no additional virus application will be performed.

In group 2 the initial administration of the IMP is via the intravenous route. Subjects receive 50% of the intended dose by 5 infusions on days 1 to 5, each infusion containing 10% of the total dose. After the last infusion on day 5 there is an observation period until day 9 and on day 10 tumor resection will be performed as in group 1. In analogy to group 1, patients receive the second half of the dose by injection in the tissue surrounding the tumor cavity after tumor removal and no further virus injections will be performed in each individual during the course of the trial.

#### Trial schedule and duration

As ParvOryx01 is a first in man trial with administration of a replication competent parvovirus the recruitement schedule for the trial is strictly regulated. Prior to the treatment of the 2nd subject of each dose level data from the 1st subject of this level will be collected up to day 28. Similarly, prior to the treatment of the 3rd subject of a dose level data from the 2nd subject up to day 18 will be collected. The 2nd and 3rd subject will only undergo treatment with the IMP if no unjustifiable adverse reactions occurred previously. The decision will be made by mutual agreement between the principal investigator or another responsible investigator and the sponsor. After completion of a dose level the data safety monitoring board (DSMB) has to give consent to move to the next dose level. A decision regarding the progress to the 2nd study group will be based on agreement between DSMB, principal investigator and sponsor after review of selected data from 1st study group obtained up to Day 28. The information obtained from 1st study group will be provided to the Competent Authority (Paul-Ehrlich-Institute) for a review. A progress to the 2nd study group will only take place if there is no objection of the Competent Authority.

The per-subject trial duration including all follow-up visits will be 6 months. After the end of the main treatment phase on day 28, 3 follow-up visits will be performed at 2, 4 and 6 months after trial inclusion. The overall duration of the clinical trial, including completion of all follow-up visits related to the efficacy of the IMP in all subjects, is scheduled to last approximately 24 months.

The treatment phase and the capture of data on the safety and tolerability of the IMP (primary objective) will be completed approximately 18 month after inclusion of the 1st study subject. The per-subject trial duration as related to the primary objective will last 28 days.

It can be assumed that the treatment and the documentation of the primary objective parameters in one dose escalation level will take approximately 3 months.

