### Statistical analysis

#### Analysis variables

The primary criterion for dose modification is the relative frequency of a dose-limiting event (DLE) at a given dose level. Toxicity of a dose is defined as the probability of this dose being associated with a DLE in a patient as indicated in the trial protocol. A dose is defined as tolerable if the probability of toxicity is lower than 33 per cent. The maximum tolerated dose is defined as the dose level with the highest posterior probability of having a toxicity not higher than 33 per cent.

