#### Statistical methods

The posterior probability for toxicity will be calculated in a logistic model, where the toxicities are parametrized as follows: *p_ij_*: toxicity for group i, level j, $\text{log}\left(p_{i1}/\left(1-p_{i1}\right)\right)=a_{i}-\beta_{i;}\text{log}\left(p_{i2}/\left(1-p_{i2}\right)\right)=a_{i}\text{log}\left(p_{i3}/\left(1-p_{i3}\right)\right)=a_{i}+\beta_{i};$ with the following prior distribution for the intercept and slope parameters:

$$\left(\alpha_{1},\beta_{1},\alpha_{2},\beta_{2}\right)\sim N\left(\left(\begin{array}{c} 0\\ 0\\ 0\\ 0 \end{array}\right),\left(\begin{array}{cccc} 4 & -.2 & 1.6 & 0\\ -.2 & 4 & 0 & 1.6\\ 1.6 & 0 & 4 & -.2\\ 0 & 1.6 & -.2 & 4 \end{array}\right)\right)$$

Whenever a subject enters the study, the dose level will be elicited by calculating the posterior probability for each dose level to be tolerable. The highest dose level that is tolerable will be allocated.

The following measurements will be subject to descriptive statistical methods: vital signs, serum levels and hematology data, H-1 PV specific antibodies, virus shedding. Progression Free Survival and Overall Survival will be listed per group and subject, showing observation time and event status.

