#### Dose escalation scheme

As long as no DLE is observed, a classic three-at-one design will be followed [22]. After the first DLE is observed one more patient will be recruited at the same dose before the dose will be determined as the maximum tolerated dose following the model outlined above. The highest dose with a median probability of tolerability being at least 33 per cent will be applied as the current MTD to the subsequent patient, following the Continual Reassessment Method [23]. If the MTD is ever to be calculated as being "dose 0", the trial ends prematurely at any time with the result that no safe dose could be established (Figure 2). Nine consecutive patients will be allocated to Group 1 before nine more patients will be allocated to Group 2. As the metaparameters α and β are assumed to be correlated between groups, results from group 1 affect the escalation scheme in group 2.

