**Figure 2 F2:**
[figure not shown]
**Dose escalation scheme of ParvOryx01 for the 1^st ^study group**. The numbers (1, 2, or 3) depict the dose level for the next patient. Red arrows denote a dose limiting event in this patient and black arrows a patient tested without an event. Trial stops at the bottom line or whenever a dose level of zero is reached.

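### After a first DLE, the model-based dose rule has no bar on skipping an untried level and is not reconciled with the stepwise DSMB gate; in group 2 it can select level 3 straight after DLEs at level 1

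*Protocol article*

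**What the plan says.** Stepwise text, in the protocol article:

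- Design: "the dose escalation will be carried out in accordance to a sequential escalating design", with safety assessed after each level.
- Trial schedule and duration: "After completion of a dose level the data safety monitoring board (DSMB) has to give consent to move to the next dose level". The sentence is not restricted to the period before a DLE.
- Intervention makes a dose increase conditional on there being no dose-limiting events. Discussion puts the first three patients of both groups on the low dose.

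Model-based text, in the same article:

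- Dose escalation scheme: three patients per level until a DLE occurs, then "After the first DLE is observed one more patient will be recruited at the same dose before the dose will be determined" by the model. The allocation rule is "The highest dose with a median probability of tolerability being at least 33 per cent will be applied as the current MTD".
- Statistical methods: "The highest dose level that is tolerable will be allocated".
- Analysis variables calls a dose tolerable if its toxicity is below 33%, and defines the MTD as "the dose level with the highest posterior probability of having a toxicity not higher than 33 per cent".
- The groups are linked through the prior, so that "results from group 1 affect the escalation scheme in group 2".

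Figure 2 shows the decision tree, but its caption reads "Dose escalation scheme of ParvOryx01 for the 1^st ^study group".

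**The concern.** The model-based text never requires that the level below has been given in the group, and it does not refer to the DSMB. The stepwise text does not say what completing a level means once the model assigns each patient singly. Neither says which rule prevails. If the gate prevails, a patient whose model dose it bars has no defined dose. If the model prevails, a level can be skipped.

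This would matter little if the model rated level 3 as worse after DLEs at level 1. With the printed prior it does not. By Table 1, the step from level 1 to level 3 is 1 × 10^6 to 1 × 10^9 pfu in total and, in group 2, 1 × 10^5 to 1 × 10^8 pfu per infusion. Both are 1000-fold, in a first-in-man trial, straight after a low-dose DLE. If the DLE falls in patient 1, patient 3 is the first to be allocated by the model, which conflicts with the low dose that Discussion promises the first three patients.

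**Working it through.** The article states no operating characteristic for the rule, so there is no figure to reproduce. The check applies the printed model.

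**Inputs (Statistical methods).** Logits of toxicity at levels 1, 2, 3 are α−β, α, α+β. Prior means are 0, Var(α)=Var(β)=4, Cov(α,β)=−0.2 within a group, and the cross-group covariance is 1.6 for α and for β. The sign of β is not restricted.

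**Why level 3 does not react.** Cov(α−β, α+β) = Var(α) − Var(β) = 4 − 4 = 0, so levels 1 and 3 are independent a priori within a group. P(β<0) is about 0.50. DLEs at level 1 can therefore be absorbed as a falling dose-toxicity slope.

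**Histories.** The first DLE falls in patient 1, 2 or 3 at level 1, and the extra patient does or does not have one. That gives six histories, written DLEs/patients.

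**Posterior P(toxicity ≤ 33%) at levels 1/2/3**, by numerical integration of the prior times the binomial likelihood:

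| Level 1 data | Group 1 | Group 2 after a DLE-free group 1 (0/3, 0/3, 0/3) |
|---|---|---|
| 2/2 | 0.02 / 0.11 / 0.40 | 0.04 / 0.25 / 0.59 |
| 1/2 | 0.30 / 0.32 / 0.40 | 0.38 / 0.53 / 0.59 |
| 2/3 | 0.11 / 0.24 / 0.40 | 0.15 / 0.42 / 0.59 |
| 1/3 | 0.49 / 0.41 / 0.40 | 0.57 / 0.61 / 0.59 |
| 2/4 | 0.24 / 0.32 / 0.40 | 0.29 / 0.51 / 0.59 |
| 1/4 | 0.64 / 0.47 / 0.40 | 0.70 / 0.67 / 0.59 |

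**Applying the criterion.** Median toxicity is at most 33% exactly when the tabulated probability is at least 0.50.

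- Group 2, median-toxicity reading: level 3 passes in all six histories (median toxicity 0.21 to 0.22), so it is chosen each time with level 2 untried.
- Group 2, MTD definition in Analysis variables (level with the largest tabulated probability): level 3 in four of six (2/2, 1/2, 2/3, 2/4).
- Group 1, median-toxicity reading: level 3 never passes (0.40 < 0.50), so no skip.
- Group 1, MTD definition: level 3 in the same four histories.

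**How often, median-toxicity reading.** The DLE rates p1/p2/p3 at the three levels are assumptions, taken as equal in both groups. Group 2 starts at level 1, as Discussion says. Enumerating all group 1 paths, only two end states lead to a group 2 skip:

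- No DLE in nine patients: A = [(1−p1)(1−p2)(1−p3)]^3.
- 1/5, 0/1, 0/3, reached only with the DLE in patient 3: B = p1(1−p1)^4(1−p2)(1−p3)^3.

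The chance of a first DLE among group 2 patients 1 to 3 is C = 1−(1−p1)^3, and the overall skip probability is (A+B) × C.

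| Assumed rates | A | B | C | (A+B) × C |
|---|---|---|---|---|
| 2/3/5% | 0.736 | 0.015 | 0.059 | 4.4% |
| 5/10/20% | 0.320 | 0.019 | 0.143 | 4.8% |
| 10/20/33% | 0.112 | 0.016 | 0.271 | 3.5% |
| 20/33/50% | 0.019 | 0.007 | 0.488 | 1.3% |

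**The case against.** A reader might infer that the protocol lets the model alone send a patient from level 1 to level 3. The documents do not support that. DSMB consent is required without condition and concerns the next level, and Design, Intervention and Discussion all describe stepwise escalation. A sensible team would probably not skip. What stands is that the two rules are printed side by side with no order of precedence and no dose for the case where they disagree.

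A reader might also infer that group 1 carries the same risk. Taken literally, a median of (1 − toxicity) of at least 33%, or a probability of tolerability of at least 33%, does give level 3 in all six group 1 histories. The first accepts toxicity up to 67%, against the 33% limit in Analysis variables; the second ignores the word median. On the median-toxicity reading there is no skip, and Figure 2, which cannot be seen here, may exclude one. So no group 1 skip is claimed. Figure 2's caption does not extend to group 2.

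Other limits also stand:

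- The group 2 result needs a nearly DLE-free group 1. A single DLE at level 3 there (0/3, 0/3, 1/3) lowers level 3 to about 0.46 and removes the skip.
- A criterion on mean toxicity, which the text does not use, would not skip (0.338 to 0.341 at level 3).
- The level 3 total dose and its intracerebral half would already have been given in group 1; only the intravenous doses would be new. Benefit/risk assessment also reports earlier human injections of roughly 2 × 10^8 to 3 × 10^10 without severe side effects, though not of GMP material.
- A full protocol may contain a no-skip clause. The conflict is nevertheless between rules that this article states.

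**Conclusion.** The point holds as an unreconciled pair of escalation rules, with a demonstrable consequence in group 2. After a DLE-free group 1, the printed model selects untried level 3 in all six first-DLE histories at level 1 on the median-toxicity reading, and in four of six on the article's own MTD definition. The trigger is not remote from the sponsor's expectations, since Benefit/risk assessment anticipates few side effects.

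The overall probability is modest: about 1 to 5% on the median-toxicity reading. Conditional on a DLE-free group 1 it equals C above, 14 to 49% for the three higher rate sets and 6% at the lowest. These figures rest on assumed DLE rates, a 0.33 cut-off and a group 2 start at level 1. The posterior probabilities rest only on the printed prior. The sponsor should correct the rule because the step is 1000-fold and the remedy is a few sentences.

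**What to change.** Add to Dose escalation scheme: the model dose is an upper limit and is subject to the gate in Trial schedule and duration. Within each group no level may be skipped. A level not yet given in the group may be used only when the level directly below is completed, that level and all lower levels are tolerable in the model, and the DSMB has consented. Otherwise the subject receives the highest permitted tolerable level, or dose 0 if there is none. In Trial schedule and duration, define completion for the model-guided phase; three treated subjects is a reasonable choice. Check Figure 2 against the new wording.

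The condition on lower levels is needed. Without it, group 2 history 2/4 would still move up 50-fold to level 2 (median toxicity 0.325) while the model calls level 1 intolerable (median 0.46).

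The change needs no new visits, staff or committee. Its price is slower escalation and more early stops after low-dose DLEs. On the median-toxicity reading after a DLE-free group 1, histories 2/2, 1/2, 2/3 and 2/4 in group 2 would stop, and 1/3 and 1/4 could go to level 2 with DSMB consent. The sponsor should confirm that stopping at 1/2 is acceptable. Restricting the slope to be positive would address the deeper cause, but it changes the model and would need its own operating characteristics; the no-skip rule works whatever the prior.
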